### 8.1 Sample size

Among 20 participants assigned to DNAX2 in EV02 30% responded to env plus at least one of gag, pol or nef. Assuming the same proportion in the DNAX2 group (control group) in EV03/ANRS Vac20, then 63 participants per group would provide 90% power to detect a difference between DNAX2 and DNAX3, if in DNAX3 the proportion responding to env plus gag/pol/nef is 60%, an absolute difference of 30%. An absolute difference of 25% (30% vs 55%) would be detected with 80% power.

It is proposed to recruit 70 to each group, 140 in total, to allow for loss to follow-up, and failure to complete the allocated regimen for other reasons.

### 8.2 Primary analysis

The immunological end-points will be considered present or absent according to standardised operating procedures which take the background activity into account ( $> 4$ -fold the negative control and  $> 55$  Spot forming units/ $10^6$  cells). In both EV01 and EV02, a small proportion ( $<5\%$ ) of subjects showed persistent IFN $\gamma$  ELISpot reactivity to peptide pools prior to vaccination and subsequently across several timepoints. Subjects with IFN $\gamma$  ELISpot reactivity to peptide pools prior to vaccination will be considered to have non-specific cross-reactive responses to the peptide pools, and will be excluded from the immunogenicity analysis. The two groups DNAX2 and DNAX3 will be compared in terms of the proportion responding to *env* plus *gag/pol/nef* using a Chi-square test.

All safety end-points will be graded by the Clinical Investigators and reviewed by the Operational Sub-Group. Any queries about grade and relationship to study product that cannot be resolved will be referred to the Trial Coordinating Committee for a final decision. For the primary analysis of safety endpoints (as defined in section 1.5.1), results will be expressed as a proportion and the two groups compared using Fisher's exact test.

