**(v) Rationale for this study**

This study is preceded by two others: EV01 and EV02. In EV01 the safety and immunogenicity of NYVAC-C x 2 was assessed. EV02, which finished in 2006, provided additional safety data to EV01 on NYVAC-C, and the first immunogenicity data in humans on the use of DNA-C as a priming agent, comparing DNA-C x2 + NYVAC-C x2 to NYVAC-C x2 alone. The highest practicable dose of DNA-C was investigated in EV02 and a significantly higher proportion of volunteers that completed the prime-boost regimen had IFN $\gamma$  ELISpot responses compared to those that received both NYVACs, 90% compared to 40% (2-sided Fisher's exact Test:  $p = 0.003$ ).

During the implementation of EV02 a consensus began to emerge that three DNA immunisations may be required for optimal priming. Data from the exploratory DNA x3 prime – Ad5 x1 boost trial supporting this hypothesis were presented at the AIDS Vaccine Conference 2006 in Amsterdam, with higher mean responses and an increase in the breadth of response with most participants responding to gag as well as *env* [26].

This study proposes to compare the DNA-C x3 prime + NYVAC-C x1 boost to the DNA-C x2 prime + NYVAC-C x2 boost in a large enough study to make a robust assessment.

The design will be open to the participants and investigators, but the laboratory personnel conducting the ELISPOT, flow cytometry and antibody assessments will be blind to allocation. The randomisation will be stratified by gender to ensure an equal proportion of women in each group.

EuroVacc 03/ANRS Vacc 20 will address the following questions:

1. Does DNA-C x 3+NYVAC-C x1 elicit broader responses to peptide pools in IFN $\gamma$  ELISpot assays compared to DNA-C x 2+NYVAC-C x2?
2. Does DNA-C x 3+NYVAC-C x1 elicit higher mean responses across the peptide pools in IFN $\gamma$  ELISpot assays compared to DNA-C x 2+NYVAC-C x2?
3. Is DNA-C x 3+NYVAC-C x1 safe compared to DNA-C x 2+NYVAC-C x2?

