### Endpoints

The primary end-points are:

- Immunogenicity: cellular responses to *env*, *gag*, *pol* and *nef* assessed using the IFN- $\gamma$  ELISPOT technique. The two treatment groups will be compared in terms of the proportion responding to *env* plus at least one of the *gag*, *pol*, *nef* peptide pools at weeks 26 or 28 using the Chi-square test.
- Safety: local (pain, cutaneous including induration), general (fever, chills, headache, nausea, vomiting, malaise, myalgia) and other unsolicited adverse events within 7 and 28 days.

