#### **3.2 Clinical history and examination**

A past medical history will be collected using the screening proforma at the screening visit, including details of any previous reaction to vaccination, history of epileptic fit, exposure to vaccinia, and contraceptive practices. The general examination will include weight (kg), height (cm) and arm and thigh circumference (see 4.1.1), blood pressure, inspection of the skin to exclude severe eczema and check for the presence of a vaccinia scar, respiratory, cardio-vascular and abdominal systems examination. An assessment of cervical and axillary lymph nodes will also be undertaken. The examination results and history of exposure to vaccinia will be recorded on the case record form. The general examination will be repeated at the final study visit.

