### 8.3 Secondary analysis

#### 8.3.1 Immunogenicity

The proportion of participants will be compared at weeks 26 and 28 according to the three categories of response, i.e 1. no response, 2. response to env or 3. response to env+gag/pol/nef or to gag/pol/nef alone as follows. The two groups (DNAX2 and DNAX3) will be compared in terms of the overall response by fitting a multinomial logistic model to the response categories and testing the significance of inclusion of the vaccine assignment in the model. This provides a global test of the null hypothesis that the proportion in the three response categories in DNAX3 is the same as in DNAX2. If this global test was significant the two groups will be compared in terms of the proportion responding to env alone and in terms of the proportion responding to gag/pol/nef (relative to no response).

If present, the response will be quantified in spot-forming units per million cells for each peptide pool at each time-point according to standardised operating procedures. For the purposes of comparison in the secondary analysis, the mean positive response for each regimen will be calculated across the peptide pools and across the following weeks:

- Weeks 26 and 28

The mean percentages CD4 and CD8 T cells responses specific to HIV peptide pools will be evaluated at weeks 26 and 28, 48 and 72 by flow cytometry. HIV specific T cell responses will be defined by the percentages of cells producing IL-2/Interferon- $\gamma$  within CD4 and CD8 T cell populations after ex-vivo stimulation with peptide pools.

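### Gender is a stratification factor, but the primary chi-square test ignores it: a valid analysis that a gender-stratified test would improve slightly

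*Protocol*

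**What the plan says.** - Protocol, Introduction (v), Rationale: "The randomisation will be stratified by gender to ensure an equal proportion of women in each group".
- Protocol, section II, Endpoints: the groups are compared on response to env plus at least one of the other "peptide pools at weeks 26 or 28 using the Chi-square test".
- Protocol, 8.2: "The two groups DNAX2 and DNAX3 will be compared in terms of the proportion responding to" env plus gag/pol/nef, "using a Chi-square test". Gender is not mentioned.
- Protocol, 8.3.1: the secondary multinomial model is described as "testing the significance of inclusion of the vaccine assignment in the model". No gender term is named.
- Protocol, 8.1: "Among 20 participants assigned to DNAX2 in EV02 30% responded to env plus at least one of gag, pol or nef". This gives the 30% control rate. The plan is 63 per group for 90% power at 30% v 60%, with 80% power stated for 30% v 55%, and recruitment of 70 per group.

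Section 8 does not mention the stratification. Section II foresees a separate analysis plan, which is not at hand. The primary test itself, however, is named in the protocol, in two places.

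**The concern.** When randomisation forces a factor to balance between groups, that factor can no longer contribute to the chance difference between them. A crude chi-square still counts the between-gender spread in response as noise. If men and women respond at different rates, the test therefore uses a variance that is too large, rejects less often than its nominal level under the null, and loses some power. A test that works within gender removes that part of the variance.

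At stake is a small amount of precision on the primary endpoint. Because the protocol fixes the unstratified test, an analysis plan that made a stratified test primary would depart from the protocol text, so the protocol is the right place to settle it.

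**Working it through.** **Inputs.** From 8.1: control rate 30%, alternatives 60% and 55%, 63 evaluable and 70 recruited per group, 1:1. Assumed, because the protocol does not state them: two-sided 5% level, half women, exact gender balance between groups, and a range of gender odds ratios.

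**1. Reproduce the protocol's figure.** For 30% v 60% the mean rate is 0.45 and the difference is 0.30.

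n' = [1.96·√(2·0.45·0.55) + 1.2816·√(0.30·0.70 + 0.60·0.40)]² / 0.30² = (1.379 + 0.860)² / 0.09 ≈ 55.7, so 56 per group without continuity correction.

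With correction: n = (n'/4)·[1 + √(1 + 4/(n'·0.30))]² = 13.92 × 2.113² ≈ 62.2, so 63. This matches the protocol and supports the assumed two-sided 5%. At 63 per group, 30% v 55% gives 81.8% uncorrected, in line with the stated 80%. These calculations do not involve gender and do not need to change.

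**2. Why the crude test turns conservative.** Under the null with an overall rate of 0.30, the crude variance uses 0.30 × 0.70 = 0.21. With gender balanced by design, the true variance uses the average of p(1−p) within gender. The gender rates are those that average 0.30 and have the stated odds ratio.

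- Odds ratio 3 (18.9% v 41.1%): (0.189·0.811 + 0.411·0.589)/2 = 0.198. Ratio to 0.21 = 0.941. Effective cut-off 1.96/√0.941 = 2.02, so size ≈ 4.3%.
- Odds ratio 5 (14.4% v 45.6%): (0.144·0.856 + 0.456·0.544)/2 = 0.186. Ratio = 0.884. Cut-off 1.96/√0.884 = 2.08, so size ≈ 3.7%.

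**3. Simulation.** 400,000 trials per setting, uncorrected Pearson chi-square against CMH without continuity correction, common treatment odds ratio across genders. Size is at a 30% rate in both groups; power is for 30% v 55%. Repeat runs agreed within about 0.2 points.

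| Per group | Gender odds ratio | Size, crude v CMH | Power, crude v CMH | CMH minus crude, power |
|---|---|---|---|---|
| 63 | 1 | 5.1% v 4.9% | 83.5% v 82.6% | −0.9 |
| 63 | 1.5 | 5.0% v about 5% | 83.6% v 83.0% | −0.6 |
| 63 | 2 | 4.7% v about 5% | 83.8% v 83.6% | −0.2 |
| 63 | 3 | 4.3% v 5.0% | 84.4% v 84.8% | +0.4 |
| 63 | 5 | 3.7% v 5.0% | 85.2% v 86.8% | +1.6 |
| 70 | 1 | not tabulated | no loss | about 0 |
| 70 | 3 | 4.4% v 4.9% | 86.4% v 87.7% | +1.3 |
| 70 | 5 | 3.8% v 4.9% | 87.3% v 90.3% | +3.0 |

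**4. Other assumptions.** With 30% or 50% women, and response differing by 0 to 30 points between genders on the absolute scale, 63 per group gives:

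- 30% v 60%: crude power 93.9–94.9%, CMH 93.1–95.3%.
- 30% v 55%: crude power 83.5–84.6%, CMH 82.5–85.5%.
- Size at a 30% rate with a 30-point gap: crude 3.8–4.0%, CMH about 5.0%.

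At a 45% rate in both groups with no gender effect, the crude size is 5.8%. That comes from the discreteness of the counts, not from leaving gender out.

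**The case against.** The case for leaving the plan alone is substantial. The stated purpose of stratifying is an equal proportion of women in each group, and that is met whatever test follows. No passage promises a gender-adjusted analysis, so nothing is contradicted. Nothing in the protocol suggests that ELISpot response differs by gender, and an odds ratio of 3 already means about 19% v 41% responding. At odds ratios of 2 or less, CMH has slightly lower power at 63 per group. All of this stands, and it keeps the point minor.

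It does not remove the point. The protocol names the primary test, so this is a stated choice and not a detail left open. The possible loss from stratifying is also smaller than the possible gain, particularly at the 70 per group to be recruited.

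A reader might go further in three ways that the documents do not support:

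- **That the reported p-value or interval is invalid because it does not match the randomisation.** The crude p-value is valid, and conservative only if gender is prognostic. Section 8.2 specifies no interval. The only confidence bound in the protocol is the conditional one for the DSMC (section II and 7.7), and its method is not given.
- **That stratifying costs nothing.** It can cost about 1 point of power at 63 per group.
- **That the primary analysis should also adjust for vaccinia exposure, because "history of exposure to vaccinia will be recorded on the case record form".** Exposure is not a stratification factor, and a supportive covariate model is ordinary analysis-plan content. Its absence here is not a fault.

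**Conclusion.** The point holds as a minor improvement. Randomisation is stratified by gender, and the primary test is fixed as one that does not use gender. Leaving gender out does not inflate the type I error through the strata, and it does not disturb the sample size. If gender is strongly prognostic, the crude test runs at roughly 3.7% to 4.3% instead of 5% and gives up 0.4 to 1.6 points of power at 63 per group, or 1.3 to 3.0 at 70. If gender has little or no effect, stratifying loses at most about 1 point at 63 and essentially none at 70.

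These sizes assume half women, exact balance, a 30% control rate, a two-sided 5% level and gender odds ratios of 3 to 5. The protocol supplies only the control rate. Whether gender is prognostic in this trial cannot be judged from the protocol.

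**What to change.** In section II (Endpoints) and section 8.2:

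- name the Cochran-Mantel-Haenszel test stratified by gender as the primary test;
- report the gender-stratified difference in response proportions with its 95% CI;
- keep the unstratified chi-square as a sensitivity analysis.

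The cost is a sentence in each of the two sections. Gender is already known from randomisation, so no new data are needed, and the 63 and 70 per group stay as they are. The price is the possible loss of about 1 point of power at 63 per group if gender turns out not to matter.

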### 8.3 Secondary analysis

#### 8.3.1 Immunogenicity

The proportion of participants will be compared at weeks 26 and 28 according to the three categories of response, i.e 1. no response, 2. response to env or 3. response to env+gag/pol/nef or to gag/pol/nef alone as follows. The two groups (DNAX2 and DNAX3) will be compared in terms of the overall response by fitting a multinomial logistic model to the response categories and testing the significance of inclusion of the vaccine assignment in the model. This provides a global test of the null hypothesis that the proportion in the three response categories in DNAX3 is the same as in DNAX2. If this global test was significant the two groups will be compared in terms of the proportion responding to env alone and in terms of the proportion responding to gag/pol/nef (relative to no response).

If present, the response will be quantified in spot-forming units per million cells for each peptide pool at each time-point according to standardised operating procedures. For the purposes of comparison in the secondary analysis, the mean positive response for each regimen will be calculated across the peptide pools and across the following weeks:

- Weeks 26 and 28

The mean percentages CD4 and CD8 T cells responses specific to HIV peptide pools will be evaluated at weeks 26 and 28, 48 and 72 by flow cytometry. HIV specific T cell responses will be defined by the percentages of cells producing IL-2/Interferon- $\gamma$  within CD4 and CD8 T cell populations after ex-vivo stimulation with peptide pools.

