| Is there a quantitative difference in the breadth of immune responses following the 3 prime regimen compared to the 2 prime regimen?                                | Wks 26, 28 IFN $\gamma$
ELISPOT
1 vs 2                                                    | The proportion of individuals in each group with CD8/CD4+ T cell responses to env plus at least one of the gag, pol, nef peptide pools                                                                                                                    |
| Secondary Questions
Is there a quantitative difference in the strength of immune responses following the 3 prime regimen compared to the 2 prime regimen? | Wks 26, 28 IFN $\gamma$
ELISPOT
1 vs 2                                                    | Mean IFN $\gamma$ ELISPOT response across peptide pools and wks 26 and 28 per group                                                                                                                                                                       |
| Is there a quantitative and/or qualitative difference in CD4 and CD8 T-cell responses following the 3 prime regimen compared to the 2 prime regimen?                | Wks 26, 28
Flow cytometry :
Intracellular
synthesis of IL-2/
IFN $\gamma$
1 vs 2 | Proportion of individuals in each group with CD4 and CD8 T cell responses to HIV peptide pools assessed by the percentage of cells producing IL-2 and/ IFN $\gamma$ . Comparisons between groups of mean percentages of HIV specific CD4 and CD8 T cells. |
| Is the 3 prime regimen safe compared to the 2 prime regimen?                                                                                                        | All weeks
1 vs 2                                                                             | Proportion of participants per group with grade 3 or above adverse events during the trial, excluding those considered unrelated to vaccine                                                                                                               |

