### 1.5.2 Secondary

Secondary immunogenicity and safety end-point information will be collected on all participants on the following:

- cellular responses
  - CD8/CD4+ T cell mean IFN $\gamma$  Spot Forming Units (SFU) per million cells across the peptide pools at weeks 26 and 28
  - CD8/CD4+ T cell mean Spot Forming Units (SFU) per million cells across the peptide pools at any week following the first immunisation including weeks 48 and 72
  - mean proportion of CD4/CD8+ T cells producing IL-2 and/or IFN- $\gamma$  following ex-vivo stimulation with HIV-1 peptide pools at weeks 26 and 28, 48 and 72
  - number of different epitopes that can be characterised
- antibody responses
  - precise assays to be determined at a later stage, but prior to unblinding of laboratory personnel
- all grade 1 and 2 adverse events
- all events including those considered unrelated

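### The ELISpot strength analysis in section 8.3.1 averages positive responses only, so it selects on a post-randomisation outcome and does not analyse the mean-SFU endpoint defined elsewhere

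*Protocol*

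**What the plan says.** Three places in the Protocol define the strength question without restricting it to positives. The second question in section I(v) asks whether three primes "elicit higher mean responses across the peptide pools". The table in section III gives the endpoint as the mean "ELISPOT response across peptide pools and wks 26 and 28 per group". Section 1.5.2 lists the mean "Spot Forming Units (SFU) per million cells across the peptide pools at weeks 26 and 28".

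Section 8.3.1 then fixes the analysis. "If present, the response will be quantified in spot-forming units per million cells for each peptide pool at each time-point", and for the between-regimen comparison "the mean positive response for each regimen will be calculated across the peptide pools and across the following weeks", naming weeks 26 and 28. Whether a response is present is settled in section 8.2: "The immunological end-points will be considered present or absent according to standardised operating procedures which take the background activity into account", the thresholds being more than 4-fold the negative control and more than 55 SFU per million cells.

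The opening of section 8 sets a modified intention-to-treat population of everyone randomised and immunised at least once. The only further exclusion for immunogenicity is ELISpot reactivity before vaccination.

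**The concern.** Positivity is measured after vaccination and is the outcome that the trial expects the regimens to change. Section 8.1 plans for env plus gag/pol/nef response in 30% v 60%. A mean over positive readings is therefore taken over differently selected readings in the two arms, and randomisation no longer protects the comparison. That holds whatever the SFU values turn out to be.

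The restriction also means that the endpoint defined in sections III and 1.5.2 is never compared between arms: section 8.3.1 contains no SFU analysis that includes non-responders or negative pools. At stake is the answer to the second of the trial's three stated questions. A regimen that raises the mean response over all participants could show no gain, or an apparent loss, on the planned summary.

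**Working it through.** **The plan's own figure.** The protocol gives no number for the strength analysis. Its sample size supplies the 30% and 60% used below, so it is reproduced first. Section 8.1 says "Among 20 participants assigned to DNAX2 in EV02 30% responded to env plus at least one of gag, pol or nef", and takes the DNAx3 case where "the proportion responding to env plus gag/pol/nef is 60%, an absolute difference of 30" percentage points. It does not state alpha; two-sided 0.05 is assumed.

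- Uncorrected n per group = [1.960 × √(2 × 0.45 × 0.55) + 1.282 × √(0.30 × 0.70 + 0.60 × 0.40)]² / 0.30² = 55.7, so 56.
- With continuity correction, n = (55.7/4) × [1 + √(1 + 4/(55.7 × 0.30))]² = 62.2, so 63.

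This matches the stated 63, and the point below does not touch it.

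**Illustration by weighted means.** Inputs:

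- gag/pol/nef responders b = 0.30 (DNAx2) and 0.60 (DNAx3), from section 8.1, all assumed also to respond to env.
- env responders 0.90 in both arms. This borrows the 90% with any ELISpot response after prime-boost in EV02 (section I(v)); applying it to env and to both arms is an assumption.
- Mean positive env reading 300 SFU and mean positive gag/pol/nef reading m. Both are assumptions, with m varied.
- Two readings per participant (env, and gag/pol/nef taken as one), negatives counted as 0.

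Positive-only mean = (0.90 × 300 + b × m) / (0.90 + b).
All-participant mean = (0.90 × 300 + b × m) / 2.

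For m = 80:

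- DNAx2: (270 + 24)/1.20 = 245 and (270 + 24)/2 = 147.
- DNAx3: (270 + 48)/1.50 = 212 and (270 + 48)/2 = 159.

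| m (SFU) | Positive-only mean, DNAx2 to DNAx3 | All-participant mean, DNAx2 to DNAx3 |
|---|---|---|
| 80 | 245 to 212 | 147 to 159 |
| 150 | 262.5 to 240 | 157.5 to 180 |
| 300 | 300 to 300 | 180 to 225 |
| 450 | 337.5 to 360 | 202.5 to 270 |

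The positive-only mean falls as b rises only when m is below 300, the assumed env mean. The all-participant mean rises in every row.

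The protocol does not say whether to average over readings or first within each participant. Averaging within participant first, at m = 80:

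- DNAx2: (0.60 × 300 + 0.30 × 190)/0.90 = 263.
- DNAx3: (0.30 × 300 + 0.60 × 190)/0.90 = 227.

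The direction is the same.

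**Simulation.** This used independent lognormal env and gag/pol/nef readings, a cut-off of 55 SFU, P(env positive) = 0.90 in both arms, P(gag/pol/nef positive) = 1/3 v 2/3 (so both positive in 30% v 60%), and 63 per group. The log-scale SDs are assumptions.

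| Log SD | Positive-only mean | All-participant mean (negatives = 0) | Trials with positive-only mean lower in DNAx3 |
|---|---|---|---|
| 0.7 | 161.8 to 160.3 (-0.9%) | 99.8 to 125.7 (+26%) | 51% |
| 1.0 | 296.0 to 288.6 (-2.5%) | 182.5 to 226.1 (+24%) | 54% |
| 1.3 | 594.6 to 567.2 (-4.6%) | 366.9 to 444.4 (+21%) | 56% |

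In the same data, a t test on each participant's mean log SFU, with everyone included, found DNAx3 significantly higher in about 92% of trials. The positive-only mean, averaged within participant and tested on the log scale, was significantly lower in DNAx3 in about 2% of trials. In this model the planned summary mostly fails to register the gain; it rarely reverses it with significance.

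**The case against.** A reader might infer that the positive-only mean must fall when a regimen broadens the response. The documents do not support that. It falls only if the added responses are weaker than the existing positive mean, and the protocol reports no SFU magnitudes. Section I(v) also cites a three-prime trial with higher mean responses as well as greater breadth. In the 80 SFU example, an env mean of 355 rather than 300 in DNAx3 removes the fall: (0.90 × 355 + 48)/1.50 = 245. This part of the objection stands. Even then the all-participant mean would rise from 147 to (319.5 + 48)/2 = 183.75, so the planned summary would show nothing where the overall mean rose by 25%.

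Secondly, breadth and strength are separate questions in section III. Breadth is tested by the primary chi-square test and the three-category model, neither limited to responders, and a responder-only mean read beside those proportions is a legitimate two-part description. That is fair for description. It does not make the mean a randomised comparison, and section 8.3.1 names it as the comparison. An all-pool mean does partly reflect breadth, but it is the quantity that sections III and 1.5.2 define.

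Thirdly, an analysis plan is foreseen and could settle details. Here, however, the protocol does not leave the summary open; it specifies one that differs from its own endpoint.

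A reader might also extend the point to flow cytometry. Section 8.3.1 does not limit those percentages to positive responses, so no such defect is shown.

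**Conclusion.** The point holds as a correction to a secondary analysis. Two parts rest on the text alone: the comparison selects on a post-vaccination outcome expected to differ between arms, and it matches neither the unrestricted endpoint nor the modified intention-to-treat population.

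The size of any distortion rests on assumed SFU values. Across the illustrations at 30% v 60%, the positive-only mean ranged from a 13% fall (245 to 212) through no change to a 7% rise (337.5 to 360), while the all-participant mean rose each time. The supportable statement is that the planned summary can fall or stay flat when the overall response rises. That it will point against the better regimen is not established. The primary chi-square test and the 63 per group are unaffected.

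**What to change.** Reword the comparison sentence in section 8.3.1:

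- For every participant in the immunogenicity analysis set with a week 26 or 28 result, average the background-subtracted SFU over all peptide pools and the available results from those two weeks, negative readings included.
- Compare the arms by Wilcoxon rank-sum test. If a log scale is preferred, state the floor used for zero or negative background-subtracted values.
- Keep the positive-only mean, labelled descriptive and shown beside the number of responders in each arm.

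The flow-cytometry analysis needs no change. The cost is a short rewording and no new data: ELISpot is scheduled for all participants at both weeks, and the positivity rule in section 8.2 already requires a reading for each pool.
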